#### Sample size, sampling and recruitment

Table 1 gives the details of the sample size calculations. To detect a difference of 4 mm Hg Systolic Blood Pressure (SBP), the individual randomization sample size has been calculated at 239 subjects per intervention arm (SD of 19.5 mm for SBP [22]), with a 80% power and an alpha of 0.05. Since, cluster randomization is being attempted in this study, the individual randomization sample size has to be adjusted by a design effect of 2.98 [design effect = 1+ (size of cluster -1) * Intra cluster Correlation (ICC)]. The ICC for the clusters among the Mahabubnagar district, AP, India (study site) has been calculated to be 0.02 (based on the Indian sentinel surveillance study done on a representative sample from 10 sites in India). Hence, the cluster adjusted sample size is 713 hypertensive patients (8 clusters with 125 subjects in each cluster to allow for a 20% loss to follow up) per intervention arm to detect a 4 mm Hg difference in Systolic Blood Pressure (SBP) with a power of 80% and an alpha of 0.05. After adjusting for the coefficient of variation among the various clusters (CV = 0.25), the sample size per intervention arm is 741, i.e. a total of 8 clusters (with equal cluster size of 100 each) would be required per intervention arm.

**Table 1 T1:** sample size calculations

**Detectable difference in SBP between both the groups**	**80% power with an ICC of 0.02**				**90% power with an ICC of 0.02**			
	**Sample size required for individual randomization per arm**	**Sample size required for cluster randomization per arm (DE = 2.98)**	**Sample size required for cluster randomization with CV = 0.25 (DE = 3.1)**	**Minimum no of clusters with a cluster size of 100**	**Sample size required for individual randomization per arm**	**Sample size required for cluster randomization per arm (DE = 2.98)**	**Sample size required for cluster randomization with CV = 0.25 (DE = 3.1)**	**Minimum no of clusters with a cluster size of 100**
4 mm of Hg	374	1115	1160	24	500	1490	1550	32
5 mm of Hg	**239**	**713**	**741**	**16**	320	954	992	20
6 mm of Hg	166	495	515	12	222	622	689	14

*ICC* = Intra Cluster correlation; *DE* = design effect; *CV* = coefficient of variation.

Randomly chosen 8 PHCs – 4 urban and 4 rural (homogenous in age and gender distribution) for each intervention arm from a district in the State of AP, India would form the study centers. Each PHC has an out patient load of 50-100 patients/day. 2- 4 hypertensive patients are being envisaged to be recruited per day by the Physician per PHC from the patients attending the out patient clinic in the PHC. 10- 20 patients per week per PHC, 20- 40 per month per PHC and 125 patients in 4-6 months. Study recruitment will last from June 2011 to Dec 2011.

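### The text claims 80% power for a 4 mm Hg difference in systolic pressure, but its sample sizes are Table 1's 5 mm Hg figures; power at 4 mm Hg is about 55–64%

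*Protocol article*

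**What the plan says.** All of this stands in the protocol article, under the heading Sample size, sampling and recruitment.

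- The starting point is 4 mm Hg: "To detect a difference of 4 mm Hg Systolic Blood Pressure (SBP), the individual randomization sample size has been calculated at 239 subjects" per arm, assuming "SD of 19.5 mm for SBP" and "with a 80% power and an alpha of 0.05".
- For clustering, "the individual randomization sample size has to be adjusted by a design effect of 2.98". The ICC behind this "has been calculated to be 0.02". The result is 713 patients "per intervention arm to detect a 4 mm Hg difference in Systolic Blood Pressure (SBP) with a power of 80% and an alpha of 0.05".
- For unequal cluster sizes: "After adjusting for the coefficient of variation among the various clusters (CV = 0.25), the sample size per intervention arm is 741". The text turns this into 8 clusters of 100 per arm.
- The section refers the reader to Table 1 for the details. At 80% power, the table's 5 mm Hg row, in bold, holds 239, 713 and 741 per arm and 16 clusters. Its 4 mm Hg row holds 374, 1115 and 1160 per arm and 24 clusters. The cluster counts in the table cover both arms.

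The abstract (Methods) reports 1600 participants already recruited: 800 per arm, in eight clusters of 100.

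**The concern.** The same three sample sizes are tied to 4 mm Hg in the text and to 5 mm Hg in the table, at the same power and alpha. Both cannot be right. Required sample size varies with the inverse square of the difference, so moving from 5 to 4 mm Hg multiplies it by (5/4)² = 1.56.

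This is the power statement for the only primary endpoint. A reader who trusts the text would think that a true 4 mm Hg benefit had a 20% chance of being missed, when the design's chance of missing it is about twice that. The abstract says the results will inform policy makers and the Conclusion ties scale-up to them, so a non-significant result could be taken as stronger evidence against a 4 mm Hg effect than it is.

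**Working it through.** **Inputs, all from the sample-size section unless noted.** SD 19.5; alpha 0.05 (sidedness is not stated, but two-sided reproduces Table 1); power 80%; ICC 0.02; cluster size 100; CV of cluster size 0.25; loss to follow-up 20%; 800 recruited per arm in 8 clusters (abstract).

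**Step 1: individually randomised size per arm.**

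n = 2 × SD² × (1.96 + 0.8416)² / d², with 2 × 19.5² = 760.5 and 2.8016² = 7.849.

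| d (mm Hg) | n per arm | rounded up | Table 1 |
|---|---|---|---|
| 4 | 373.1 | 374 | 374 |
| 5 | 238.8 | 239 | 239 |
| 6 | 165.8 | 166 | 166 |

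The table is reproduced exactly. The text's 239 appears only at 5 mm Hg.

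**Step 2: cluster adjustment.** The design effect is 1 + (100 − 1) × 0.02 = 2.98. With CV 0.25 it is 1 + ((1 + 0.25²) × 100 − 1) × 0.02 = 3.105, which the table shows as 3.1.

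| d (mm Hg) | × 2.98 | × 3.1 | clusters of 100 per arm | both arms |
|---|---|---|---|---|
| 5 | 239 × 2.98 = 712.2 (713) | 239 × 3.1 = 740.9 (741) | 8 | 16 |
| 4 | 374 × 2.98 = 1114.5 (1115) | 374 × 3.1 = 1159.4 (1160) | 12 | 24 |

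Every figure in the text's chain is therefore a 5 mm Hg figure.

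**Step 3: could another assumption give 239 at 4 mm Hg?** A one-sided alpha of 0.05 still needs 294 per arm. Reaching 239 two-sided would require an SD of about 15.6, against the stated 19.5. Neither explains the text.

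**Step 4: power at 4 mm Hg for the recruited design.** Effective n per arm = N / design effect; SE = 19.5 × √(2 / effective n); power = Φ(4/SE − 1.96). The last column uses a noncentral t with 14 degrees of freedom (16 clusters minus 2).

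| Analysed per cluster | N per arm | Design effect | Effective n | SE | Power, normal | Power, t with 14 df |
|---|---|---|---|---|---|---|
| 100 | 800 | 3.105 | 257.6 | 1.718 | 64.4% | 58.2% |
| 80 (after 20% loss) | 640 | 2.68 | 238.8 | 1.785 | 61.1% | 55.0% |

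For 80 per cluster the design effect is 1 + (1.0625 × 80 − 1) × 0.02 = 2.68.

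**Step 5: more favourable assumptions (normal approximation).** Dropping the CV adjustment with 800 per arm gives 66%. Analysing 125 in every cluster with no loss gives 67% with the CV adjustment and 69% without it. None of these comes near 80%.

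**Step 6: the difference the design can detect at 80% power (normal approximation).** 2.8016 × 1.718 = 4.8 mm Hg with 800 analysed per arm, and 2.8016 × 1.785 = 5.0 mm Hg with 640.

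**The case against.** The strongest reply is that this is a wrong digit in two sentences. The section sends the reader to Table 1, the chosen row is in bold, and the recruited design matches that row. On this view the trial was planned for 5 mm Hg and nothing in its conduct is affected. That may well be so, and it is why the correction is cheap. The wrong digit is nevertheless the stated target difference for the primary endpoint and it appears twice, so it has to be corrected.

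A second reply is that the lower figures of 55% and 58% come from a t reference which the article does not specify, whereas Table 1 uses the normal approximation. This is fair as a matter of labelling: on the article's own method the range is 61–64%. The t figures show what a cluster-level analysis with only 16 clusters would give. The same reference also lowers power at 5 mm Hg, to 77% with 100 per cluster and 74% with 80, so 80% power at 5 mm Hg holds only on the normal approximation.

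A third reply is that the document does not say whether 4 or 5 mm Hg was intended. That is true. The bold row, the cluster count and the recruited numbers all point to 5. If 4 was intended, the consequence is worse, because the design falls well short of its target. The text needs correcting in either case.

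Finally, a null result should be read from its confidence interval, not from planned power. That is good practice, but it does not make a false power statement acceptable.

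**Conclusion.** The text is wrong as written. The figures 239, 713 and 741 per arm, with 8 clusters per arm, give 80% power for 5 mm Hg, as Table 1 shows, and not for 4 mm Hg. For the recruited design, power at 4 mm Hg is 61–64% on the normal approximation and 55–58% on a t reference with 14 degrees of freedom. The chance of missing a true 4 mm Hg effect is thus about 36–45% instead of 20%. Eighty per cent power at 4 mm Hg would need 1160 per arm (12 clusters per arm, 24 in all), against the calculated 741 per arm (8 clusters per arm, 16 in all).

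These figures rest on the article's own SD, ICC and CV, a two-sided alpha of 0.05, and 80 to 100 patients analysed per cluster. The contradiction between text and table depends on none of the power calculations.

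**What to change.** Change 4 to 5 mm Hg in both sentences of the sample-size section, so that the text agrees with Table 1 and the recruited design. Add the power at 4 mm Hg for 8 clusters of 100 per arm, naming the method: about 61–64% by normal approximation, or 55–58% with t on 14 degrees of freedom. Say that the 80% figure at 5 mm Hg is by normal approximation. Label sample sizes as per arm and the table's cluster counts as both arms. When a non-significant result is reported, give 5 mm Hg as the planned detectable difference, alongside the confidence interval.

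The sponsor should confirm that 5 mm Hg was the planning target. If it was 4 mm Hg, the article should say plainly that the recruited design does not reach 80% power for it.

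The cost is wording, plus a slightly less favourable stated detectable difference. No patients, clusters or procedures change.

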**Methods:**

The trial design is a cluster randomised community intervention trial, in which the participants would be adult male and female hypertensive patients, in the age group of 35 to 64 years, reporting to the Primary Health Care centres of Mahabubnagar district, Andhra Pradesh, India. The objective of the study is to test the effectiveness and compare the cost effectiveness and cost utility among hypertensive subjects randomized to receive either decision support system or a chart based algorithmic support system in urban and rural areas of a district in the state of Andhra Pradesh, India (baseline versus 12 months follow up). The primary outcome would be a comparison of the systolic blood pressure at 0 and 12 months among hypertensive patients randomized to receive the decision support system or the chart based algorithmic support system. Computer generated randomisation and an investigator and analyser blinded method would be followed. 1600 participants; 800 to each arm; each arm having eight clusters of hundred participants each have been recruited between 01 August 2011 - 01 March 2012. A twelve month follow up will be completed by March 2013 and results are expected by April 2013.

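### The 125-per-cluster allowance for 20% loss was not recruited, and the sample size ignores the small number of clusters, so the stated 80% power has no margin at 5 mm Hg and is about 74–79% on an unadjusted t reference

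*Protocol article*

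**What the plan says.** All planning figures are in the protocol article, under Sample size, sampling and recruitment.

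- **Planned recruitment.** The text gives "8 clusters with 125 subjects in each cluster to allow for a 20% loss to follow up", that is 1000 per arm recruited and 800 left to analyse. The recruitment paragraph repeats the target for each centre: "125 patients in 4-6 months".
- **Cluster size one sentence later.** After the adjustment for CV, the text says that "a total of 8 clusters (with equal cluster size of 100 each) would be required per intervention arm".
- **Recruitment achieved.** The abstract (Methods) states: "1600 participants; 800 to each arm; each arm having eight clusters of hundred participants each have been recruited". The twelve-month follow-up was still to be completed.
- **Inputs.** The variability is given as "SD of 19.5 mm for SBP". The ICC is 0.02 and the CV 0.25. The error rates are fixed "with a 80% power and an alpha of 0.05". The inflation for clustering is stated as "design effect = 1+ (size of cluster -1) * Intra cluster Correlation (ICC").
- **Target difference.** The text reads "To detect a difference of 4 mm Hg Systolic Blood Pressure (SBP), the individual randomization sample size has been calculated at 239 subjects per intervention", but Table 1 places 239, 713 and 741 in the 5 mm Hg row.

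**The concern.** The figure of 100 per cluster serves two purposes. In the plan it is what remains after loss; in the abstract it is what was recruited before any loss. The article does not remark on the change and does not restate power.

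Separately, the centre is the unit of randomisation and there are 8 per arm, so an unadjusted comparison between arms has at most 14 degrees of freedom. The printed sample sizes take no account of that.

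A reader faced with a null result would suppose that the trial had 80% power with a 20% loss already provided for. That bears directly on whether the result is read as evidence of no useful effect.

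**Working it through.** **1. Reproduce the plan's figure.** With two-sided normal quantiles, n per arm = 2 × (1.96 + 0.8416)² × 19.5² / 5² = 238.8, so 239. The design effect at m = 100 is 1 + 99 × 0.02 = 2.98. With CV, DE = 1 + [(1 + 0.25²) × 100 − 1] × 0.02 = 3.105, printed as 3.1. Then 239 × 2.98 = 712 (713 printed) and 239 × 3.1 = 741. Dividing, 741/100 = 7.4, rounded up to 8 clusters per arm. The 5 mm Hg row is reproduced with normal quantiles and no correction for the number of clusters. The article does not say whether alpha is two-sided, but two-sided reproduces its numbers.

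**2. Apply the article's 20% loss to the recruited clusters.** 100 × 0.8 = 80 per cluster, and 8 × 80 = 640 per arm. The design effect must be recomputed at the new size: 1 + [1.0625 × 80 − 1] × 0.02 = 2.68. The number needed at that size is 238.8 × 2.68 ≈ 640.

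**3. Power at each size.** SE = 19.5 × √(2 × DE / (8m)).

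- m = 100: SE = 19.5 × √(2 × 3.105/800) = 1.718; 5/1.718 = 2.910.
- m = 80: SE = 19.5 × √(2 × 2.68/640) = 1.785; 5/1.785 = 2.802.

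Normal power is Φ(5/SE − 1.96). The t figures use the noncentral t with 2 × 8 − 2 = 14 df.

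| Difference | Analysed per cluster | CV | Normal | t, 14 df |
|---|---|---|---|---|
| 5 mm Hg | 100 | 0.25 | 82.9% | 77.2% |
| 5 mm Hg | 80 | 0.25 | 80.0% | 74.1% |
| 5 mm Hg | 100 | 0 | 84.4% | 78.9% |
| 5 mm Hg | 80 | 0 | 81.5% | 75.7% |
| 4 mm Hg | 80 | 0.25 | 61.1% | 55.0% |

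**4. Separate the two causes (5 mm Hg, CV 0.25).** Loss costs 82.9 − 80.0 = 2.9 points on normal quantiles. The t reference costs a further 80.0 − 74.1 = 5.9 points. Had 125 per cluster been recruited and 100 analysed, the t figure would have been 77.2%, still under 80%.

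**5. Detectable difference with 80% power (t, 14 df, CV 0.25).** About 5.2 mm Hg at 100 per cluster and 5.4 mm Hg at 80.

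**6. Sensitivity to baseline adjustment.** The baseline to 12-month correlation r is not given, so these values are assumptions. Multiplying the variance by 1 − r² at both levels, with 80 per cluster, CV 0.25 and 14 df, gives 78.0% at r = 0.3, 81.1% at r = 0.4 and 85.2% at r = 0.5.

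**The case against.** The strongest reply is that the missing allowance does not by itself bring power below 80%, and this stands. A reader might set the 640 left after loss against the printed 741 and infer a shortfall. That comparison mixes two cluster sizes: 741 applies at 100 analysed per cluster, and at 80 the requirement is about 640, which is met.

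A reader might also infer that the recruited sample has no slack at all. It has some, because 7.4 clusters were rounded up to 8, giving 800 against 741. That slack, with the smaller design effect, absorbs the full 20% loss by the article's own method.

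The second reply is that 74% should not be read as the trial's power, and this also stands. The article states no analysis model, which may properly be left to the full protocol or analysis plan. The figure supposes an unadjusted comparison, CV 0.25 and a 20% loss that is planned, not observed. The abstract reports recruited clusters of 100 each, and equal sizes give 76–79%. SBP is measured at baseline, and adjusting for it could restore 80%. In the other direction, a division-stratified analysis (11 df, 72.3%) or a matched-pair analysis (7 df, 67.3%) would lower the figure, but only if it removed no between-cluster variance. The documents do not settle this.

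Neither reply removes the conflict between 125 and 100, or the absence of a small-cluster correction from a calculation that rests on 16 clusters.

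**Conclusion.** The point holds in a limited form. The planned 125 per cluster was not recruited, and the article leaves the two figures unreconciled. At 5 mm Hg the recruited sample still gives about 80% after 20% loss on normal quantiles, but with no margin. The fall below 80% comes from the t reference on 14 df: about 74–79% unadjusted, depending on loss (0 to 20%) and CV (0.25 or 0). These figures rest on SD 19.5, ICC 0.02, 8 clusters per arm and even loss across clusters.

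The documents do not support the stronger conclusion that 80% power at 5 mm Hg is out of reach, since the gain from baseline adjustment is unknown. For the 4 mm Hg named in the text, the unadjusted figure after 20% loss is about 61% (normal) or 55% (t). The conflict between 4 and 5 mm Hg is a separate and larger error in the same section.

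**What to change.** 1. Reconcile 125 with 100: state that 800 per arm were recruited and that the 125-per-cluster allowance was not applied.
2. Restate power with a t reference on the cluster degrees of freedom: about 74–79% at 5 mm Hg unadjusted or, at CV 0.25, 80% for about 5.2 mm Hg (no loss) to 5.4 mm Hg (20% loss).
3. Give the assumptions beside the figure (SD, ICC, CV, loss, degrees of freedom, no adjustment). Add that adjustment for baseline SBP could return power to 80% or more if the correlation is about 0.4 or higher, marked as an assumption.

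The cost is a few sentences and a less favourable stated power. No patients or clusters are added.

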#### Ethical principles

The participants would be given sufficient time to understand the contents of the PIS (containing the study purpose, duration, study procedures, right to withdrawal from the study, details of patient confidentiality, ethical committee clearances, the study team details), and encouraged to ask questions regarding any aspects of the study procedures that they have not understood. The written informed consent form will be read out aloud in the native language to the study participants. They will be given an opportunity to seek clarifications on any issues that have not been understood. The signatures would be obtained by the Physician who would be recruiting the hypertensive patients for the study. The Physician would also sign and date the informed consent form. One copy would be given to the patients and one copy would be retained at the study site.

## Discussion

Hypertension exerts a substantial burden on cardiovascular health status and health care systems in India. Treatment however can be costly and health care providers are interested in both whether treatments can offer improvements in disease burden and whether they represent value for money. Economic evaluations seek to resolve this issue by producing results that can be used to inform and assist the decision maker in allocating scarce health care resources. DSS have been in place in the developed world to achieve a balance between quality and cost of chronic disease health care. To the best of the author’s knowledge, there have been no randomized studies on DSS to enable policy makers to find out the effectiveness, cost effectiveness and cost utility analysis (CUA) of DSS for hypertensive patients in India. The cluster randomised community trial aims to test a decision support system among Indian hypertensive patients. Most of the previous studies on decision support system have focused on physician performance, adherence and on preventive care reminders. The uniqueness of the proposed study lies in finding out the effectiveness of a decision support system on patient related outcomes.

There are no known risks attributable to DSS per se. If the participant is receiving DSS, the software assisting the Physician prompts him or her to prescribe a particular class of drug to manage and control blood pressure. If the participant is receiving the chart based algorithmic support system, the decision to start or continue a drug is entirely up to the Physician’s judgement. The software will be developed and pilot tested and will be based on standard Indian Hypertension society guidelines (2007), which have been endorsed by the Association of Physicians of India and the Indian Cardiological Society. Adverse events that may arise due to the drugs will be monitored and any serious adverse events will be notified to the ethical committee within 24 hours. Should any serious adverse events arise the participants would be given the necessary care in the primary health care centre and if necessary will be transferred to the Rural Hospital. Substitution of the drugs causing adverse events is left to the decision of the Physician. Blood will be drawn by a qualified and an experienced phlebotomist, with due precautions. The quality of life questionnaire would be adapted from WHO BREF questionnaire which has been validated in India. Patient confidentiality will be maintained at data entry and data analysis stage.

## Conclusion

This cluster randomised community trial aims to test effectiveness, cost effectiveness and cost utility analysis of a decision support system among Indian hypertensive patients in comparison to a chart based algorithmic support system (that will have the guidelines and lifestyle advices printed as a poster format). The utility of DSS in management of hypertension will be tested in this pilot study. Subsequent scale up of DSS and future studies of DSS in management of different domains of cardiovascular diseases are envisaged based on the results of this pilot study.

## Ethical approval

Approved by the (1) Human Biology Research Ethics Committee, University of Cambridge, United Kingdom and (2) Institutional Ethics Committee, Public Health Foundation of India, New Delhi, India.
